#### Outcomes and definitions

The primary outcome is live birth, defined as the delivery of one or more living infants at ≥22 completed weeks of gestation or with a birth weight >500 g. Live birth will be confirmed and recorded based on hospital medical records and clinical documentation. For multiple pregnancies, the delivery of one or more live-born infants from the same pregnancy will be counted as one live birth event at the participant level for the primary outcome, while the number of live-born infants and plurality will be recorded separately. Pregnancy losses, including miscarriage and stillbirth, will be recorded separately and will not be classified as live birth events.

#### Data collection and management

Figure 2 summarizes the measurements collected at each scheduled visit.

**Figure 2 fig2:**
[figure not shown]
Schedule of measurements. S/B, Screening/baseline; W 4, Week 4; W 8, Week 8; W 12, Week 12; G, Gestation; P, Parturition; HADS, Hospital Anxiety and Depression Scale; PSQI, Pittsburgh Sleep Quality Index; IPAQ-SF, International Physical Activity Questionnaire Short Form; FFQ, Food Frequency Questionnaire.

#### Demographic information

Data will be collected on participants’ age, ethnicity, marital status, educational background, menstrual history, reproductive history, living environment, lifestyle factors, employment status, smoking status, alcohol consumption, and relevant characteristics of their spouses.

#### Physical measurements

Body weight and composition will be assessed using an InBody analyzer or body fat scales. Waist circumference will be measured once at the midpoint between the lowest rib and the iliac crest, while hip circumference will be measured once at the widest part of the buttocks. Blood pressure (BP) will be measured once with the participant seated and at rest for at least 10 min.

#### Questionnaires

The modified Ferriman–Gallwey score (mF-G score) of 4 will be used to detect hirsutism (14). The Hospital Anxiety and Depression Scale (HADS) is a widely used self-report questionnaire for assessing emotional distress, specifically anxiety and depression (56). It consists of 14 items, with seven assessing anxiety and seven assessing depression. Each item is rated on a 4-point scale ranging from 0 to 3. A total score above 8 suggests mild symptoms, while a score above 10 indicates moderate symptoms (57). The Pittsburgh Sleep Quality Index (PSQI) is a commonly used self-report measure of sleep quality and disturbances over a one-month period. The global PSQI score ranges from 0 to 21, with higher scores indicating worse sleep quality; a score ≥5 indicates poor sleep quality (58). Physical activity will be assessed using six items from IPAQ-SF, which captures the frequency and duration of vigorous activity, moderate activity, and walking. Data are used to classify participants into high, moderate, or low physical activity groups. Time spent in each activity category is weighted by energy expenditure to calculate MET-minutes per week (51, 52). Dietary intake over the past 12 months will be assessed at baseline using a validated semi-quantitative 25-item food frequency questionnaire (FFQ-25), which has been validated for evaluating habitual dietary consumption in Chinese populations (59–61). Participants will be asked to report the frequency (daily, weekly, monthly, yearly, or never) and quantity (using the standard Chinese unit liang, where 1 liang = 50 g) of consumption for each food item over the past 12 months (62). To objectively assess changes in dietary intake during the 12-week intervention period, three 24-h dietary recalls (covering two weekdays and one weekend day) will be extracted by dietitians from uploaded app-based food diary records of participants. Daily dietary intake will be calculated based on the reported food types and portion sizes, using the nutrient composition data from the Chinese Food Composition Table (55).

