#### Secondary

To compare the effects of a CR diet and metformin on secondary reproductive outcomes and changes in anthropometric, metabolic, and reproductive hormone parameters prior to OI in women with PCOS and overweight/obesity. Key secondary outcomes include pregnancy-related outcomes, body weight, glucose and insulin-related measures, lipid profiles, and reproductive hormone levels.

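### The HADS severity cut-offs are attached to a total score, although the scale is described as separate seven-item anxiety and depression sets

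*Protocol article*

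**What the plan says.** All of the scoring text is in the Questionnaires section of the protocol article.

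- Purpose: HADS is called a "widely used self-report questionnaire for assessing emotional distress, specifically anxiety and depression".
- Structure: "It consists of 14 items, with seven assessing anxiety and seven assessing depression".
- Item scoring: "Each item is rated on a 4-point scale ranging from 0 to 3".
- Severity: "A total score above 8 suggests mild symptoms, while a score above 10 indicates moderate symptoms", with a literature reference (57) for the cut-offs.

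The section gives no numerical range for HADS and defines no separate anxiety or depression score. The sleep index described next, by contrast, gets both a stated range and a named global score.

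On the role of HADS, the legend of Figure 2 (schedule of measurements) lists "HADS, Hospital Anxiety and Depression Scale", but the figure itself is not shown. The secondary aims state: "Key secondary outcomes include pregnancy-related outcomes, body weight, glucose and insulin-related measures, lipid profiles, and reproductive hormone levels". HADS is not on that list, and the Statistical analysis section does not mention it.

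**The concern.** The scale is introduced as measuring two things, with seven items for each, and the only severity rule is then given for a single total. An analyst following the text would add up all 14 items and label the sum. Two consequences follow.

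1. The label does not say which condition it refers to. A given total can be all anxiety, all depression or a mixture.
2. The same number is a much lower bar on a 0–42 score than on a 0–21 score. If the cut-offs were derived for a seven-item set, the labels would be given too readily.

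At stake is the meaning of any HADS categories the trial reports. The Introduction names anxiety and depression as associated with PCOS and treats the syndrome as partly psychological, so readers may take such categories at face value. The primary result is not affected.

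**Working it through.** **Inputs from the Questionnaires section:** 14 items, split 7 and 7; item scores 0 to 3; cut-offs above 8 and above 10, worded for a total. No HADS mean, SD or distribution is given anywhere in the article.

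**Step 1: ranges.** Whole scale: 14 × 3 = 42. Each set: 7 × 3 = 21.

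**Step 2: how strict the cut-offs are on each score.** With integer scores, above 8 means at least 9 and above 10 means at least 11. The mean item score needed is the lowest qualifying score divided by the number of items.

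| Cut-off | On the 0–42 total | On a 0–21 set | Ratio |
|---|---|---|---|
| Above 8 | 9/14 = 0.64 per item | 9/7 = 1.29 per item | 0.5 |
| Above 10 | 11/14 = 0.79 per item | 11/7 = 1.57 per item | 0.5 |

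As a share of the maximum, the cut-offs sit at 8/42 = 19% and 10/42 = 24% of the total, against 8/21 = 38% and 10/21 = 48% of a set.

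**Step 3: direction.** Neither set can score below 0, so a score above 8 on either set forces the total above 8. The total rule therefore flags every woman that a per-set rule with the same numbers would flag. It can also flag others: 5 on anxiety plus 4 on depression gives 9 (mild), and 6 plus 5 gives 11 (moderate), with neither set above 8. The largest total with neither set above 8 is 8 + 8 = 16, so totals of 9 to 16 can carry a label without either set passing the cut-off. This holds whatever the score distribution.

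**Step 4: how many women (illustration on assumed values).** Use a normal approximation with continuity correction, P(total > 8) = 1 − Φ((8.5 − m)/s), where m is the assumed mean total and s the assumed SD, from 5 to 7.

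| Assumed mean total | P(total > 8) |
|---|---|
| 4 | 18–26% |
| 6 | 31–36% |
| 8 | 46–47% |
| 10 | 58–62% |
| 12 | 69–76% |
| 14 | 78–86% |

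For example, m = 4 and s = 5 give 1 − Φ(0.90) = 0.18, and m = 14 and s = 5 give 1 − Φ(−1.10) = 0.86. The proportion passes one half only when the assumed mean exceeds 8.5. The approximation is crude at low means, because real scores cannot fall below 0.

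For comparison, take equal means m/2 in the two sets and a correlation of 0.6, so that the SD of one set is s/√(2 × 1.6). The chance that one given set exceeds 8 is then 1–5% at a mean total of 4, 5–13% at 8, and 30–35% at 14.

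**The case against.** The strongest reply is that the article nowhere says 8 and 10 are cut-offs for a seven-item set. The reference cited for them is not available here, and total score may be loose wording for the total of each set. This stands, and it limits the point: the article does not prove that the cut-offs are on the wrong score. It does not remove the point, because as printed the rule means a 14-item sum, and one label for that sum does not fit the two-construct purpose given in the same paragraph. If each set was meant, the wording needs the same correction.

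It can also be said that the sentence only describes the instrument. No plan to classify or compare women by these cut-offs is stated, HADS is outside the named key secondary outcomes, and the visits and arms at which it is measured cannot be checked without Figure 2. This stands too, and it is why the point is minor. There is no responder rule here to criticise.

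The narrow mild band (9–10) is no argument against the total, since the same cut-offs on a seven-item set leave the same two values. Nor is any bias between arms shown: one scoring rule would apply to both.

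**Conclusion.** The point holds as a minor scoring defect. The only HADS severity rule is attached to a total, which is at odds with the description of two separate sets. Read literally, it sets a per-item threshold exactly half that of a seven-item set and yields a label that cannot separate anxiety from depression. These conclusions need only the item counts and item scoring in the article.

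Two stronger readings are tempting and are not supported:

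- A reader might infer that most women would be labelled symptomatic. That needs a HADS distribution the article does not give. The illustration runs from 18% to 86%, and most applies only if the mean total is above about 8.5.
- A reader might infer that the trial could not tell anxiety from depression at all. That is true of a label based on the total, not of the data: the seven items of each set can be summed separately.

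**What to change.** In the Questionnaires section:

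1. Define two HADS scores, anxiety and depression, each the sum of its seven items (0–21), and compare each between arms wherever HADS is measured after baseline.
2. Check the source cited for the cut-offs, state which score they belong to, and apply them only to that score.
3. If a 0–42 total is reported, give it as a continuous score without a severity label.

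This costs a few lines of wording. The items are those already described, so it needs no new data, visits or sample size.

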#### Indexes of endocrine and metabolic function

Fasting plasma glucose, fasting insulin, 75 g oral glucose tolerance test (OGTT), insulin release test (IRT), liver and kidney function, blood lipids, thyroid function, and 25-hydroxyvitamin D will be assessed. For the OGTT and IRT, blood samples will be collected at 0 (fasting) and 2 h after glucose ingestion to assess glucose and insulin responses. Glucose concentrations will be measured using a glucose oxidase–based enzymatic assay. Serum lipid profiles, including total cholesterol and triglycerides, will be quantified via standard enzymatic colorimetric methods. Serum insulin concentrations and thyroid function parameters—thyrotropin, free triiodothyronine, and free thyroxine—will be determined using validated immunoassays. Liver function parameters, including alanine aminotransferase and aspartate aminotransferase, as well as serum uric acid, will also be analyzed using enzymatic methods. 25-hydroxyvitamin D concentrations will be assessed by mass spectrometry.

#### Sex hormone levels

LH, follicle-stimulating hormone, prolactin, T, estradiol, progesterone, 17α-hydroxyprogesterone, SHBG, and FAI will be measured using validated immunoassays, at both baseline and post-intervention.

The data sources for this study will consist of medical records and follow-up documentation, which will be systematically entered and securely maintained using an electronic data capture (EDC) system. Outcome ascertainment will be performed by assessors blinded to treatment allocation using standardized medical records and follow-up documentation. To ensure data integrity and accuracy, a three-tiered quality control framework will be implemented. Firstly, the EDC system will integrate automated real-time validation checks to evaluate logical consistency and completeness of the entered data. Secondly, clinical researchers will perform source data verification, while trained data entry personnel will be responsible for accurate data input and timely updates, thereby minimizing human error. Thirdly, an independent Data Monitoring Committee (DMC) consisting of clinical, statistical, and ethical experts will conduct periodic audits to oversee data quality and compliance with study protocols. Any identified discrepancies will be promptly flagged within the system, and the respective data entry staff will be notified to investigate and rectify these inconsistencies in a timely manner.

#### Statistical analysis

The primary analysis will follow the intention-to-treat principle, with all randomized participants analyzed according to their originally assigned treatment group regardless of intervention adherence or protocol deviations. For continuous baseline characteristics, normality will be assessed using frequency histograms and the Shapiro–Wilk test. If normally distributed, data will be presented as mean ± standard deviation (SD); otherwise, median and interquartile ranges (IQRs) will be reported. Student’s t-test or the Wilcoxon rank-sum test will be used to compare differences between groups, as appropriate. For categorical variables, frequencies and percentages will be reported for both groups. Additionally, the number of recruited participants, those lost to follow-up, protocol violations, and other relevant descriptive statistics will be documented.

The primary outcome, live birth rate, will be compared between the two groups using Pearson’s chi-square test or Fisher’s exact test for unadjusted analyses. The unadjusted risk ratio (RR) and 95% confidence interval (CI) will be estimated. In addition, an adjusted analysis will be performed using multivariable Poisson regression or a log-binomial model, as appropriate, to estimate the adjusted RR and 95% CI. Prespecified clinically relevant baseline prognostic factors that are routinely available across the study population, including age, baseline body mass index (BMI), and relevant baseline PCOS-related reproductive and metabolic characteristics, will be considered in the adjusted model. Hazard ratios (HR) and 95% CI will be calculated using multivariable Cox proportional hazards analysis to compare time to live birth between groups, with adjustment for relevant prespecified baseline prognostic factors. Pregnancy rates will also be assessed using an intention-to-treat approach with Kaplan–Meier estimation, where time to pregnancy is defined as the number of days from randomization (intervention start) to the first positive pregnancy test. Between-group differences will be evaluated using the log-rank test, and multivariable Cox proportional hazards models will be applied to adjust for the prespecified baseline prognostic factors. As anti-Müllerian hormone (AMH) measurements are not available for all participants, AMH will not be included as a covariate in the primary adjusted analysis. Among participants with available AMH measurements, supplementary exploratory analyses will be conducted to assess the association between baseline AMH and reproductive outcomes and to explore whether baseline AMH modifies the relative effects of the CR diet and metformin.

For the primary outcome, participants who are lost to follow-up and whose live birth status cannot be ascertained will be conservatively classified as not having achieved a live birth. The number and reasons for withdrawal and loss to follow-up will be documented and reported separately for each treatment group. Missing baseline covariate data will be handled using complete-case analysis in the corresponding adjusted models. Multiple imputation will be used in sensitivity analyses to assess the robustness of the results to missing covariate data. Additional sensitivity analyses will be performed to evaluate the potential impact of missing outcome data and loss to follow-up on the primary findings. These analyses will examine alternative assumptions regarding outcomes among participants lost to follow-up and will be compared with the primary analysis in which missing live birth outcomes are classified as no live birth.

Participants with insufficient intervention adherence or protocol deviations will remain included in the primary intention-to-treat analysis according to their randomized treatment assignment. Additional sensitivity analyses will be conducted to assess the potential impact of major protocol deviations on the primary findings. A per-protocol analysis will be conducted as a supportive secondary analysis and will include participants who complete the trial, meet the prespecified intervention-specific adherence criteria, and have no major protocol violations. Primary and secondary outcomes will be compared between treatment groups within the per-protocol population. The per-protocol findings will be interpreted as supportive analyses alongside the primary intention-to-treat results. Secondary outcomes will be compared between groups using a similar approach for categorical variables. Mixed-effects models will be applied for repeated measurements. Exploratory subgroup analyses will be conducted according to prespecified baseline characteristics, including age and BMI. Potential heterogeneity in intervention effects across these characteristics will be assessed by including treatment-by-subgroup interaction terms in the corresponding regression models. Where AMH measurements are available, the potential effect-modifying role of AMH will also be explored in supplementary analyses.

All statistical analyses will be performed using SAS version 9.4 (SAS Institute Inc., Cary, NC, USA). All tests will be two-tailed, and a *p*-value < 0.05 will be considered statistically significant.

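### Complete-case handling of missing baseline covariates leads the adjusted live-birth and Cox analyses and drops randomised women whose outcome is known; the imputation already planned should lead instead

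*Protocol article*

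**What the plan says.** All references are to the protocol article, section Statistical analysis, unless stated.

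- Analysis population: "The primary analysis will follow the intention-to-treat principle, with all randomized participants analyzed according to their originally assigned treatment group".
- Live birth rate "will be compared between the two groups using Pearson’s chi-square test or Fisher’s exact test for unadjusted analyses", with an unadjusted risk ratio (RR).
- The model-based estimate follows: "In addition, an adjusted analysis will be performed using multivariable Poisson regression or a log-binomial model". Its covariates are age, baseline BMI and an open group: "relevant baseline PCOS-related reproductive and metabolic characteristics, will be considered in the adjusted model". They are described as factors routinely available in the study population.
- Time to live birth is described only through a multivariable Cox model. Time to pregnancy has Kaplan–Meier estimates and a log-rank test as well as a multivariable Cox model.
- AMH is left out as a covariate because it is not available for everyone. The sentence saying so refers to a primary adjusted analysis.
- Missing outcome: women lost to follow-up "whose live birth status cannot be ascertained will be conservatively classified as not having achieved a live birth".
- Missing covariates: "Missing baseline covariate data will be handled using complete-case analysis in the corresponding adjusted models". The next sentence adds: "Multiple imputation will be used in sensitivity analyses to assess the robustness of the results to missing covariate data".

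**The concern.** The complete-case rule is a written choice, not a detail left to an analysis plan. It has three consequences.

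1. Information is discarded unevenly. A woman whose live birth is unknown stays in and counts as a failure. A woman whose live birth is documented, but who lacks one baseline laboratory value, leaves the adjusted models.
2. The unadjusted and adjusted RRs are estimated on different women. If they differ, a reader cannot tell whether adjustment or exclusion is responsible.
3. For time to live birth, the main described analysis has no version that includes all randomised women. They return only through the imputation sensitivity analysis.

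Nothing is gained in exchange. Baseline values precede allocation, so imputing them without reference to arm or outcome keeps everyone and does not bias the comparison.

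**Working it through.** **1. The plan's own figure.** Inputs from Sample size: control rate 31.0%, difference 15.0 points (so 46%), two-sided alpha 5%, power 80%, dropout 20%, 1:1 allocation. With unpooled variance:

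n per arm = (1.960 + 0.842)² × (0.31×0.69 + 0.46×0.54) / 0.15² = 161.27, rounded up to 162.

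162 / (1 − 0.20) = 202.5, rounded up to 203 per arm, total 406. The stated figure reproduces exactly.

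**2. Who is kept where.**

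| Analysis | Needs covariates? | All 406 kept? |
|---|---|---|
| Live birth, chi-square or Fisher test and unadjusted RR | No | Yes; missing outcome counts as no live birth |
| Live birth, adjusted RR | Yes | Only if covariates are complete |
| Time to pregnancy, Kaplan–Meier and log-rank | No | Yes |
| Time to pregnancy, Cox | Yes | Only if covariates are complete |
| Time to live birth, Cox (no unadjusted version described) | Yes | Only if covariates are complete |

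**3. Women lost from the adjusted models.** The article gives neither a missingness rate nor the number of covariates, so every rate here is an assumption.

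- *Gaps fully coincide* (the same women lack everything): loss = 406 × m. At 2%, 3% and 5% this is about 8, 12 and 20 women.
- *Gaps independent across k covariates:* loss = 406 × [1 − (1 − m)^k].
  - 4 covariates at 2%: 1 − 0.98⁴ = 7.8%, or 32 women.
  - 6 covariates at 3%: 1 − 0.97⁶ = 16.7%, or 68 women.
  - 8 covariates at 5%: 1 − 0.95⁸ = 33.7%, or 137 women.

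Independence is the pessimistic end, because values from one blood draw tend to be missing together.

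**4. What that costs.** Approximate power at 31% v 46%, with n = 203 × (1 − fraction dropped) per arm:

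power = Φ{[0.15√n − 1.960√(2×0.385×0.615)] / √(0.31×0.69 + 0.46×0.54)}

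Relative confidence-interval width is 1/√(1 − fraction dropped).

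| Dropped | Women | Power | Relative CI width |
|---|---|---|---|
| 0% | 0 | 87.7% | 1.00 |
| 2% | 8 | 87.0% | 1.01 |
| 5% | 20 | 86.0% | 1.03 |
| 10% | 41 | 84.1% | 1.05 |
| 20% | 81 | 79.6% | 1.12 |

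These figures ignore loss to follow-up and any gain from adjustment. If 20% of each arm were lost and counted as no live birth, the rates would become 24.8% v 36.8% (0.8 × 31% and 0.8 × 46%). Power would then be 74.7% with nobody dropped, 72.5% with 5% dropped and 65.0% with 20% dropped. The increment due to complete-case handling is similar at 5% and somewhat larger at 20%.

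**The case against.** A reader might infer that the plan contradicts its own intention-to-treat rule. The text does not support that. The rule is attached to the primary analysis. The first-listed live-birth comparison needs no covariates and keeps everyone, and the adjusted model is introduced as an addition. This stands. What it leaves open is that the article never names one estimate as the single primary one, refers elsewhere to a primary adjusted analysis, and gives time to live birth no unadjusted analysis.

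A reader might also infer bias between arms. That is not supported either. Recruitment and randomization requires baseline assessments before randomisation, and envelopes stay closed until baseline data collection is complete. Missingness should not depend on arm, so the comparison among complete cases is still a randomised one.

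Third, missingness may be low. Age and BMI are eligibility criteria, the covariates are chosen for routine availability, and AMH is excluded because it is incomplete. This argues for the low end of the range, and the larger loss figures should not be read as forecasts. But the remaining reproductive and metabolic covariates are not listed, and the authors thought gaps likely enough to write a rule and a sensitivity analysis.

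Finally, multiple imputation is already planned, so the dispute is only about which adjusted estimate leads. That is correct, and it is why the point is modest. The order still matters, because the leading estimate is the one that readers will set beside the unadjusted RR.

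**Conclusion.** The point holds in a limited form. Making complete-case analysis the main method for missing baseline covariates is an inferior choice for the adjusted RR and both Cox models. It removes randomised women with known outcomes, costs precision, and puts adjusted and unadjusted estimates on different populations. It removes none of the 406 women from the unadjusted live-birth comparison and does not confound the arms.

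The size cannot be fixed from the article. At an assumed 2–5% with coinciding gaps, about 8–20 women are lost, power at the design rates stays at 86% or above, and confidence intervals widen by at most about 3%. Power drops just below 80% only when about 20% are dropped, which would need gaps scattered over many covariates. The case for change rests mainly on the better method being already planned and nearly free, not on a large expected loss.

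**What to change.** In the adjusted RR model and both Cox models, keep every randomised woman by imputing missing baseline covariates as the main adjusted analysis. Either of two routes will do:

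- simple imputation that uses neither arm nor outcome (overall or centre mean) with a missing-value indicator; or
- the multiple imputation already planned, promoted from sensitivity to main adjusted analysis.

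Move complete-case analysis to sensitivity, and report how many women it excludes in each arm.

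Cost: a change of wording and slightly more analysis work. The imputation code is needed anyway. Sample size, data collection and the unadjusted comparison do not change.
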